## **2 Background and justification**

### **2.1 Trial of Improved Practices**

In order to support countries in their efforts to address problems of food insecurity and malnutrition, FAO has been promoting improved complementary feeding in several countries in the past years by teaching families how to enrich young children's diets using locally available nutrient-dense foods. In Afghanistan and Zambia, FAO has assisted the Ministries of Agriculture and Health to improve complementary feeding through formative research using Trials of Improved Practices (TIPs – see box below). This approach has been especially set up by FAO to identify improved recipes and ideal messages for programming to improve feeding practices of women or caretakers of infants and young children. While all complementary feeding recipes and recommendations developed during TIPs are targeted to children 6 months of age and higher, it is important to note that exclusive breastfeeding up to 6 months of age is recommended during the TIPs process (1). It is part of FAO's efforts to integrate nutrition into agricultural and rural development activities and to foster linkages between the health and agricultural sector. Recommended dietary practices (including improved local recipes) have now been published in separate manuals for Afghanistan (2) and Zambia (3). Participatory cooking demonstrations using nutritionally improved recipes in conjunction with dietary counseling at household level to optimize young children's dietary intake have been introduced in various community development projects in these countries. FAO programs using the TIPs approach to improve infant and young child and family nutrition are ongoing in Malawi, Laos and Cambodia.

---

 Afghanistan, Cambodia, Lao People's Democratic Republic and Zambia

**Box: What are Trials of Improved Practices (TIPs)?**

TIPs are a formative research technique used in programs that promote change. The methodology has been well tested and validated, particularly with regard to health and hygiene behavior, and has been used in various countries to develop nutrition behavior change communication strategies, including infant and young child feeding practices(4-6).

Using TIPs, program planners gain an in depth understanding of families' preferences and capabilities, as well as the obstacles they face in improving their nutrition and their motivations in trying new behaviors and practices. TIPs therefore allow program planners to pre-test, adapt and evaluate the actual practices and recommendations in line with local circumstances and needs for eventual dissemination and promotion on a larger scale.

The TIPs can be divided into the three steps:

1. Investigation of food security, family feeding and child feeding practices, development of preliminary list of improved feeding recommendations and training of TIPs facilitators,
2. TIPs implementation: participants explore how to improve their child's health and nutrition,
3. TIPs evaluation and development of detailed plan for disseminating acceptable and feasible feeding recommendations and recipes

Preliminary evidence from FAO programs that have employed TIPs to improve infant and young child feeding have demonstrated the following:

- families' interest in using an increased variety of locally available nutrient-dense foods accessible in different seasons to improve the nutritional adequacy of complementary foods,
- the relevance of introducing basic nutrition, child feeding and food selection and preparation skills, and
- the acceptability and practical feasibility of using improved complementary feeding recipes in the family setting.

The recipes were designed to meet the Recommended Daily Allowances (RDA) of children 6 to 23 months with affordable locally available foods using the WHO Guiding Principles for Complementary Feeding of the Breastfed Child (1). However, due to the absence of rigorous impact evaluation studies, up to now there is only

---

 Currently zinc recommendations for children 12-24 month cannot be met with locally available foods. Further clarification is needed why recommendations are up to 10 x higher for 12-24 month old children compared to 6-11 month old children.

anecdotal evidence of the impact of these improved complementary foods and feeding recommendations on feeding practices, children's dietary diversity, nutritional intake and anthropometric status identified through TIPs within a FAO project.

## **2.2 Background information Cambodia**

According to the Global Hunger Index report 2011(7) Cambodia was able to improve its status from extremely alarming to serious. With 28% of the population living below the international poverty line of 1.25 US\$ per day, Cambodia remains vulnerable to natural disasters, volatile food prices and following this food insecurity (7, 8). The coverage with sanitation facilities and the access to improved drinking water sources continues to be low with 18% of the rural population using improved sanitation facilities and 61% using improved drinking water sources. The literacy rate among the 15 to 24 years old in the population is almost 90% (8).

Globally more than one third of child deaths are related to undernutrition (9, 76). In Cambodia the under-five mortality rate declined since 1990 but still remains high with 51 deaths per 1,000 live births in 2010 (8). In the Southeast Asian region, Cambodia shows higher prevalence of stunting, wasting and underweight among infants than other countries in the region (9). Rural Cambodian children under five show a higher prevalence for underweight with 30% than urban children with 19% (8). Factors contributing to child undernutrition are among others low birth weight, infectious diseases, maternal underweight and insufficient breastfeeding and complementary feeding practices. (10, 74-76)

Focusing on anthropometric data of length/height for age (Height-for-Age Z-Scores), the values decrease dramatically after two months of age (11, 12). Around the globe Asian countries show the most intense stunting rates with a mean value between 1.5 to 2SD below the WHO Growth Standard (13). According to the Cambodian Demographic and Health Survey 2010 (10) a total of 40% of children are stunted. 46% are younger than two years and 10% of the stunted children are younger than six months (Table 1).

---

 The Global Hunger Index (GHI) 2011 refers to data collected from 2004 to 2009. The GHI categorizes countries by giving scores for the proportion of undernourished in the population, child mortality and child underweight. The scores then allow a distribution of the countries according to their hunger situation into five groups: low, moderate, serious, alarming, and extremely alarming.

Low birth weight is defined by the WHO as a weight below 2500g, for a given time period. (74)

**Table 1: Prevalence of stunting of children < 5 years in Cambodia**

| DHS 2010           | Prevalence of stunting (%)
(Height for age Z-Score <-2SD)  |                       | n     |
|--------------------|---------------------------------------------------------------------------|-----------------------|-------|
|                    | HAZ <-3SD                                                                 | HAZ<-2SD  |       |
| Children < 5 years | 13.6                                                                      | 39.9                  | 3,975 |
| < 6months          | 5.1                                                                       | 10.4                  | 294   |
| 6-8 months         | 5.9                                                                       | 20.5                  | 230   |
| 9-11 months        | 6.2                                                                       | 18.7                  | 191   |
| 12-17 months       | 9.3                                                                       | 32.0                  | 412   |
| 18-23months        | 13.7                                                                      | 46.7                  | 414   |

 WHO Child Growth Standards 2006 (13)

 Includes children who are below -3 SD from the WHO Child Growth Standards population median

Following the WHO guidelines for complementary feeding of the breastfed and non-breastfed child (1, 73), a child should be exclusively breastfed for the first six months of life and from six months to 23 months a child should be given complementary foods in addition to breastmilk. This period in life is often referred to as a critical window because inadequate nutritional diets affect growth and vulnerability towards illness (5, 11, 76). Important factors are the early initiation of breastfeeding and the continuation of exclusive breastfeeding up to six months (14). The complementary diet should consist of at least four out of the seven food groups each day (dietary diversity) and should be at least fed for the minimum number of times per day (minimum meal frequency). Dietary diversity and minimum meal frequency result in a necessary minimum acceptable diet for children from six to 23 months. According to the CDHS 2010 73.5% of children below six months are exclusively breastfed. Almost 10% received breastmilk and plain water. The mean duration of exclusive breastfeeding in Cambodia is 4.9 months. 96% of breastfed children from six months to two years of age were given solid or semisolid complementary foods in addition to breastmilk. Complementary food in Cambodia is mainly a watery rice-based porridge called *borbor* (14).

Less than one-third of the under twos in Cambodia meet the minimum criteria for dietary diversity and only about 50% received the minimum number of meals according to the WHO guidelines (1, 10).

### 2.2.1 MALIS Project in Cambodia

In 2012 the 'Improving Food Security and Market Linkages for Smallholders (MALIS)' project will be launched in two provinces in Northern Cambodia, Otdar Meanchey and

PreahVihear, as a further continuation of the FAO EU Food Facility Project from 2009 which was implemented in ten provinces in the country. Funded by the Food Security Thematic Program(FSTP) of the EU the “Improve the Food Security of Farming Families Affected by Volatile Food Prices” project was implemented from 2009 to 2011 in 50,000 farming households who were affected by volatile food prices. The project objective was based on five aims:

- Improved agricultural productivity
- Reduce post-harvest losses
- Improve fish production and fish resources management
- Improved water resources and irrigation
- Improve dietary diversity and family feeding (focus on Infant and young children)

The target group consists of vulnerable rural families who are depending primarily on agriculture for their livelihood. With the overall objective to improve the food security and nutrition situation of the target group, a close collaboration between the Ministry of Agriculture, Forestry and Fisheries (MAFF) and local NGOs is planned. The program addresses some of the countries objectives towards food security and agricultural development as well as the Millennium Development Goal 1 and 3 (MDG) to eradicate hunger and extreme poverty in Cambodia(16). The enhancement of income, agricultural productivity and nutritional status are among the main objectives as well as the promotion of the resilience to external shocks for vulnerable smallholder farmers in targeted provinces.

As one fourth of the Cambodian population is undernourished (17), the former project also included a nutrition component. Following the TIPs formative research technique (see Chapter 2.1), the project paid special attention to the lack of knowledge in Infant and Young Child Feeding (IYCF) Practices. TIPs was conducted in 360 households of 4 villages in each of the nine provinces, one trial in the wet season (Aug - Sept 2010) and one trial in the dry season (Dec 2010 - Jan 2011). Each trial was followed by a cooking demonstration for at least 9,000 households. As a result of TIPs culturally acceptable complementary feeding practices were collected and are available for dissemination.

With a new fund from the FSTP of the EU the present MALIS project is implemented in previous and new areas of two former target provinces, Otdar Meanchey and

PreahVihear. These provinces are considered to have a best fit to the framework established by the EU for targeting assistance under the certain program.

The expected outcome of MALIS nutrition component is that the capability of target households is to be strengthened to the extent that the diets of children below two years meet their nutritional needs by the end of the project.

## **2.3 Rationale of the study**

FAO needs to document the impact of the TIPs approach, capitalize on lessons learnt and refine recommendations to inform the design of future interventions and prioritize resource allocation. However, FAO is not a research institution and has therefore asked the Justus Liebig University to evaluate their TIPs approach within ongoing FAO food security projects i.e. MALIS in Cambodia as well as the FAO/FICA project in Malawi. The expected outcome is an assessment of the effectiveness of promoting locally-available and affordable complementary foods to improve infant and young children's nutritional status based on TIPs within FAO food security projects.

## **3 Literature Review**

### **3.1 Malnutrition and the role of food security for improving nutrition**

The burden of undernutrition in many developing countries continues to be high and slows the potential for individual, social and economic development. High rates of wasting and stunting among children under-five years of age are a reflection of the serious challenges many developing countries are facing: inadequate access to and availability of healthy and diverse foods, improper feeding and caring practices, as well as poor health and hygiene conditions (18-21). The food and financial crises of 2008 and 2009 have brought governments' attention to the importance of addressing food and nutrition security as a fundamental component of socio-economic development and political stability. This trend is reflected by efforts to reform the Committee on World Food Security, the creation of the High-Level Task Force on

---

 The Committee for World Food Security (CFS) is the United Nations' forum for reviewing and following up on policies concerning world food security. It also examines issues which affect the world food situation. It was established as a result of the food crisis of the 1970s, upon recommendation from the 1974 World Food Conference.

Food Security as well as donors' renewed interest in food and nutrition security (EU Food Facility; Spanish MDG-Fund on Children, Food Security and Nutrition; USAID's Feed the Future; World Bank Scaling Up Nutrition (SUN) Framework, and the 63rd World Health Assembly Resolution on Infant and Young Child Feeding). Growing attention is given to the role of agriculture and to the linkages between agriculture and health in improving nutrition.

The conceptual framework of nutrition (figure 1) shows the different impact factors on nutrition security as well as food and health security, which may be applied on individual, regional and national level.

[figure not shown]

Figure 1: Adopted UNICEF framework of underlying causes of malnutrition and mortality (22,23).

The linkage between food production and nutritional health can only be achieved if the interactions among food diversity on the plate, people's nutritional knowledge and preferences, socio-economic factors, and crop diversity are considered (24).

 At the end of April 2008 the United Nations' Chief Executives Board established a UN System High Level Task Force (HLTF) as a temporary measure to enhance the efforts of the UN system and International Financial Institutions in response to the Global Food Security Crisis.

There has been a demand for in depth research in these areas for many years (25) in order to inform policy makers and programms to ensure funds made available for nutrition interventions are optimally utilized (26).

### **3.2 The importance of complementary feeding**

Several reviews of nutrition interventions (11, 12, 27, 28) have shown that increased attention needs to be given to complementary feeding interventions targeted to children aged 6-23 months, which is the period with the peak incidence of growth faltering, micronutrient deficiencies and infectious diseases in developing countries (11). The effects of poor nutrition resulting in stunting may also be associated with delayed motor and mental development (29, 30). Therefore, effective interventions that are preventing and reducing stunting during this vulnerable period should be a high priority.

Several interventions, targeting this age group, put the emphasis mainly on micronutrient supplementation and food supplements, as well as therapeutic feeding and care (31-46). A metaanalysis looking at the impact of micronutrient interventions revealed a limited positive effect on height gain per year with less than 0.1 cm/year through either single or multiple nutrient supplementation compared to controls (40). However, studies focusing on complementary feeding support and educational strategies have shown to have a larger impact. Pooled analysis of three studies focusing on nutritional education in food-secure populations showed an increase in mean Height for Age Z-score (HAZ) of 0.25 (95% CI 0.01-0.49) compared to the control group. The effect was even higher in studies in food insecure populations receiving food supplements with or without education (HAZ change 0.41, 95% CI 0.05-0.76) (12). An evaluation study in Haiti comparing the impact of recuperative and preventive health services to comparable households in the Haiti Demographic Health survey on linear growth confirmed these results. In addition, the study showed that the preventive program had had a greater impact than the recuperative program compared to the respective control group (mean HAZ difference: 0.341; 95% CI 0.104, 0.577 and mean HAZ difference: 0.183; 95% CI: -0.022, 0.388 respectively) (47).

Comprehensive food-based approaches that promote a variety of nutrient-dense local foods to improve children's dietary intake and nutritional status are essential (18,48). Food-based approaches that focus on the use of locally available,

affordable, and accepted nutrient-dense foods and recipes are designed to empower local populations to optimally use their resources and limit their dependency on external resources. Therefore, these approaches have a higher potential to improve child nutrition in the longer term compared to programs that mainly rely on donor funding and the distribution of micronutrients or food supplements.

## 4 Hypothesis

Assuming that behavior change messages on breastfeeding and complementary feeding practices as well as hygiene aspects as generated by the TIPs are widely accepted and out into practice by the mothers with children ages 0-23 months the data assessment will be based on the following hypotheses:

1. The Height for age Z-Score (HAZ) of children below 2 years will increase if TIPs recommendations and recipes are locally available and accepted. At conclusion of the intervention, there will be a difference of 15% of the HAZ between interventions and controls:

$$H0: \mu \text{ HAZ (intervention)} = \mu \text{ HAZ (control)}$$

$$H1: \mu \text{ HAZ (intervention)} > \mu \text{ HAZ (control)}$$

2. Secondly, prevalence of anemia, vitamin A deficiency as well as morbidity rates will be reduced:

a) Anemia (A) among children between 6 and 23 months, defined as hemoglobin level of < 11g/dl, will decrease by 25 %:

$$H0: P(A| \text{intervention}) = P(A| \text{control}),$$

$$H1: P(A| \text{intervention}) < P(A| \text{control})$$

b) Retinol binding protein (RBP) levels will decrease by 15% among children with a C-reactive protein (CRP) level of < 12mg/l:

$$H0: \mu \text{ RBP (intervention)} = \mu \text{ RBP (control)},$$

$$H1: \mu \text{ RBP (intervention)} < \mu \text{ RBP (control)}$$

c) Prevalence of children with presumed acute respiratory infections and fever (ARI) and diarrhea (D) in the last two weeks prior the survey will decrease by 25%:

$$H0: P(ARI| \text{intervention}) = P(ARI| \text{control}),$$

$$H1: P(ARI| \text{intervention}) < P(ARI| \text{control})$$

$$H0: P(D| \text{intervention}) = P(D| \text{control}),$$

$$H1: P(D| \text{intervention}) < P(D| \text{control})$$

d) There will be differences in knowledge of age-appropriate complementary feeding (KCF) of children between caretakers measured using a knowledge score in interventions and controls.

H0:  $\mu$  KCF (intervention) =  $\mu$  KCF (control),

H1:  $\mu$  KCF (intervention) >  $\mu$  KCF (control).

e) TIPs formative research generates nutritionally improved, culturally acceptable and affordable recipes which result in improved feeding practices and food intake which will result in a higher dietary diversity score for the children.

There will be differences in dietary diversity (DD) between interventions and controls:

H0:  $\mu$  DD (intervention) =  $\mu$  DD (control),

H1:  $\mu$  DD (intervention) >  $\mu$  DD (control).

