## **5 Objectives**

The purpose of this study is to observe the impact of promoting improved complementary feeding recipes and messages developed through TIPs on children's nutritional status and identify changes in complementary feeding practices in the two districts, OtdarMeanchey and PreahVihear, in Cambodia. The overall aim of the study is to evaluate the effectiveness of the wider dissemination of improved infant and young child feeding practices developed by TIPs to improve child nutritional status. The primary objective of the study is to show that children below two years have improved Height for Age Z-scores (HAZ) after at least 18 months of complementary feeding intervention, compared to children in matched control areas. Secondary objectives are to investigate whether children in the intervention area have improved nutritional status measured by vitamin A and iron status and improved health status measured by incidence of acute respiratory infection (ARI) and diarrhea compared to children in matched control areas.

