## 6.4 Sample size for baseline and impact survey

The appropriate sample size for the cross-sectional baseline survey will be determined largely by three factors (52):

- a) estimated prevalence of the variable of interest,
- b) desired level of confidence, and
- c) acceptable level of error.

Using ENA for Smart sample size calculator (49) and considering a population size of 15000 children under two in the surveyed area, 50% of stunting (key indicator), desired precision of +/- 5% and a design effect of 3 the sample size calculation results in 1124 children. Avillage is the cluster unit.

The cross-sectional impact survey sample size will be based on the formula proposed by Haynes and Moulton for cluster randomized trials Haynes and Moulton (50):

$$n = (z_{\alpha/2} + z_{\beta})^2 \frac{(\sigma_0^2 + \sigma_1^2)}{(\mu_0 - \mu_1)^2}$$

The sample size calculation resulted in 335 children for each treatment arm, considering a power of 80%, confidence level of 95%,  $\sigma_0 = 1.5$  and  $\sigma_1 = 1.2$  and estimated 15% increase of HAZ ( $\mu_0 = -1.96$ ,  $\mu_1 = -1.66$ ).

Nevertheless, to adjust for intra-class correlation (ICC), a design-effect should be included. The design effect (DEFF) is defined as:

---

Values have been estimated from the available literature.

$$DEFF = 1 + ICC (m-1)$$

Considering that  $m=19$  children per cluster (village) will be measured, and an estimated ICC of 0.03 is applied (see annex 10.3), the  $DEFF= 1 + 0.03*18=1.54$ . Multiplying the DEFF-value with the above calculation this results in 516 children below two for each treatment arm. Adding an extra 10% to account for drop-outs or non-responders results in a sample size of 568 children below two years for each treatment arm.

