## **6.8 Data collection**

The data collection in the cross sectional surveys will be based on an adaptation of the SMART methodology (49). The SMART methodology includes a questionnaire designed to assess mortality, nutritional status and food security in crisis situations. The final questionnaire will consist of standardized modules extracted from the questions designed by the SMART initiative, FAO, WHO, GIZ, and the Manoff Group (1, 6, 49, 54,55-59). Thus, mothers/caretakers with children below two years will be interviewed about their socio-economic situation, food security, mothers' and children's food intake, care, time availability, access to health, water and sanitation, motor milestones, and access to FAO food security activities by trained enumerators. Anthropometric measurements will be taken from mothers, their children below two years of age, and, if possible from fathers, by a nutritionist especially trained in anthropometric measurements. Capillary blood samples will be taken from the surveyed mothers (Hb only) and children below two years to assess the micronutrient status (retinol binding protein (RBP), transferrin receptor (TfR), hemoglobin as well as the morbidity status (C-reactive protein (CRP), acyl glycoprotein (AGP) by medical trained research staff.

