| Project Impact:
Child nutritional status is improved

Research objective:
Evaluate the impact of the project on child nutritional status in FAO food security projects                                | Key Impact Indicators: 
 
Improved child nutritional status:
 
Reduced Stunting
 
Reduced Anemia
 
Reduced vit A deficiency
 
                                                                                                                 | Baseline and Impact
Surveys of children 0-23 months in FAO food security project and non-project areas | Households are willing to participate in all aspects of data collection                                                                                                                                                |
| Outcome:
Complementary feeding (CF) practices and dietary intakes of children 0-23 months are improved

Research objective:
Assess changes in CF practices across intervention and control households | 
 
Improved CF practices (Selected WHO IYCF)
 
Decreased prevalence of anemia, vit A deficiency
 
Increased diversity of foods fed to children 6-23 months
 
Increased frequency of feeding semisolid/solid foods
 
Mothers' behavior score
 
 | One level of assessment: (Impact assessment)                                                              | The complementary feeding components are implemented according to plan and the TIPs correctly assess the decision making processes at household level that lead to sustained changes in feeding practices              |

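### Hypothesis 2b points the wrong way: it predicts a fall in mean RBP, the trial's vitamin A marker, although the protocol aims to reduce vitamin A deficiency

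*Protocol*

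**What the plan says.** Section 4 (Hypothesis) introduces its second group of hypotheses with the statement that "prevalence of anemia, vitamin A deficiency as well as morbidity rates will be reduced". Item 2b, in that group, then states that "Retinol binding protein (RBP) levels will decrease by 15% among children with a C-reactive protein (CRP) level of < 12mg/l". The formulas beneath set the null as equal mean RBP in the two arms and the alternative as mean RBP lower in intervention than in control.

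The rest of the protocol describes the vitamin A aim as an improvement:

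- Section 1 names vitamin A deficiency as a secondary outcome.
- Section 5 (Objectives) looks for "improved nutritional status measured by vitamin A and iron status" in the intervention area.
- Annex 10.1 (Logical Framework) lists "Reduced vit A deficiency" among the key impact indicators.

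The role of RBP is also stated. Section 6.8 says that children's blood is taken "to assess the micronutrient status (retinol binding protein (RBP), transferrin receptor (TfR", among other markers. The clinical checklist in the annexes describes the child's blood test as one for vitamin A and iron status.

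**The concern.** If RBP stands for vitamin A status and the intervention is meant to reduce deficiency, mean RBP should be higher in the intervention arm. Item 2b says the reverse, in its sentence and in its formula. Item 2b is also the only formal between-arm vitamin A comparison in the protocol; section 6.6 plans only a descriptive prevalence of deficiency. No correctly directed vitamin A hypothesis exists elsewhere to fall back on.

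At stake is how a named secondary outcome is interpreted. Taken literally, higher RBP in the intervention villages fails to support the hypothesis and lower RBP supports it. If the sign is changed only after the impact survey has been analysed, the change will look data-driven even though it corrects an obvious slip.

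A smaller point concerns the same sentence. It limits the comparison to children with CRP below 12 mg/l at the survey. Section 6.8 lists CRP as a morbidity marker, and item 2c expects acute respiratory infection and diarrhoea to fall by 25%. The subset is therefore defined by something measured after randomisation that the intervention may shift.

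**Working it through.** **Is there a figure to reproduce?** None for RBP: the protocol gives no RBP mean, standard deviation, power or sample size. The only powered outcome is HAZ. With the section 6.4 inputs and a difference of 15% of 1.96 = 0.294,

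n = (1.960 + 0.842)² × (1.5² + 1.2²) / 0.294² = 7.849 × 3.69 / 0.0864 = 335.1,

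which matches the stated 335 per arm. (The rounded means, with a difference of 0.30, give 322.) No RBP quantity enters this, so correcting 2b leaves it unchanged.

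**Directions in section 4, side by side.**

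| Item | Quantity compared | Better direction | Alternative for intervention |
|---|---|---|---|
| 1 | mean HAZ | higher | higher |
| 2a | prevalence of anaemia | lower | lower |
| 2b | mean RBP | higher | **lower** |
| 2c | prevalence of respiratory infection, diarrhoea | lower | lower |
| 2d | mean knowledge score | higher | higher |
| 2e | mean dietary diversity | higher | higher |

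Five of the six items pair the sign correctly with the benefit. Item 2b is the only one that uses a lower-than sign for the mean of a favourable marker. The likely cause is that the decrease and the sign were carried over from the prevalence items around it. Because words and formula in 2b agree, a symbol garbled in PDF conversion is not a plausible explanation.

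**What the alternative as written does.** Let θ be the true rise in mean RBP divided by its standard error. A test directed at lower RBP rejects the null with probability Φ(−z − θ), where z = 1.645 at a 5% directional level and 1.960 at 2.5%. The protocol names neither level for RBP, so both are shown.

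| True rise (standard errors) | 5% level | 2.5% level |
|---|---|---|
| 0 | 5.0% | 2.5% |
| 0.5 | 1.6% | 0.7% |
| 1 | 0.4% | 0.15% |
| 2 | 0.013% | 0.004% |
| 2.8 | 0.0004% | 0.0001% |

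For a true fall of 2.8 standard errors, the same test rejects with probability Φ(2.8 − 1.645) = Φ(1.155) = 88%, or Φ(2.8 − 1.960) = Φ(0.84) = 80%.

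**Illustration for a true 15% rise.** Assumptions not in the documents: RBP coefficient of variation (CV) 20% to 50%, effective sample size 150 to 335 per arm. Then θ = 0.15 / (CV × √(2/n)):

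- CV 50%, n = 150: θ = 0.15 / 0.0577 = 2.60
- CV 20%, n = 335: θ = 0.15 / 0.01545 = 9.71

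As written, at the 5% level, the chance of rejection is at most Φ(−1.645 − 2.60), about 0.00001. With the sign reversed it is Φ(2.60 − 1.645) = 83% or more. A two-sided 5% test has power of Φ(2.60 − 1.960) = 74% or more. The direction of 2b, and not the sample size, is what blocks confirmation.

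**The CRP restriction.** The documents give no share of children above 12 mg/l, no expected CRP difference between arms and no relation between CRP and RBP. The size of any selection effect cannot be calculated.

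**The case against.** The strongest reply is that nobody would apply 2b mechanically. Sections 1 and 5, the lead sentence of item 2 and annex 10.1 all make the intended direction clear, and section 6.6 would report the prevalence of vitamin A deficiency next to any RBP comparison. A two-sided test could also detect higher RBP. This stands in part. It means that an improvement would be visible in the data, and that an inability to confirm it follows only from the literal directional alternative. It does not remove the contradiction: a two-sided result showing higher RBP would still run against the stated hypothesis.

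A second reply is that the lower-than sign may have been meant for the prevalence of low RBP, in line with the lead sentence. That is possible, and it is why two remedies are offered. It does not rescue 2b, which speaks of levels and compares means.

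A reader might also infer more than the documents support:

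- *That the directional alternatives conflict with the HAZ sample size.* Section 6.4 uses the α/2 quantile, "considering a power of 80%, confidence level of 95"%. One could conclude that a one-sided 5% test doubles the benefit-direction error from 2.5% to 5%, or that 264 per arm would have been enough. But the protocol nowhere specifies a one-sided 5% test. A directional alternative with the α/2 quantile is consistent with a one-sided 2.5% test, whose error in that direction equals that of a two-sided 5% test.
- *That the CRP limit invalidates the randomised comparison.* No item predicts a change in CRP itself, only item 2c concerns infection, and no bias can be sized. Correcting RBP for CRP and AGP also conditions on markers measured after randomisation, so it is not clearly superior. The concern is legitimate but secondary.

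**Conclusion.** The point holds for the direction of hypothesis 2b. As written, it contradicts the aim of its own group of hypotheses and three other places in the protocol. A true rise in RBP cannot support it, and a true fall would. This follows from the sign and holds whatever the sample size; the probabilities above only illustrate it.

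The conclusion rests on one assumption that the protocol does not spell out: that higher RBP means better vitamin A status. This is standard subject knowledge and is implied by the protocol's use of RBP as its vitamin A marker.

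The scope is limited to one secondary hypothesis. The primary HAZ outcome, its sample size, the randomisation and the data collection are untouched. The CRP restriction is a subordinate, unquantified remark, and the verdict does not depend on it. The correction is nonetheless necessary, because a formal hypothesis for a named secondary outcome is wrong as stated.

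**What to change.** Amend item 2b in one of two ways, whichever the investigators intended:

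1. State that mean RBP will increase, with the alternative that mean RBP is higher in intervention than in control. The 15% should be reconfirmed as a target for a rise, since the protocol gives no basis for it.
2. State that the prevalence of vitamin A deficiency will be lower in intervention than in control, keep the lower-than sign, and define deficiency by an RBP cut-off, as item 2a already does for anaemia with haemoglobin. The 15% would then need restating as a change in prevalence.

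As an optional addition, report an RBP analysis of all children beside the CRP-restricted one, for example with inflammation correction using CRP and AGP, and give the number excluded by the CRP limit in each arm.

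The cost is a short dated amendment, made before the impact-survey data are analysed, and at most one extra regression. CRP, AGP and RBP come from the same assay under section 6.8.4, so no new data or blood are needed.
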